The main secondary study parameters include QoL, disease severity (NYHA functional class determination following standardized protocol; LVEF using echocardiography), and exercise capacity (six-minute walk test; see also Table 1). Other secondary variables are designed to determine whether randomization was successful, to assess their potentially moderating influence on adherence, and to generate risk profiles of patients who may or may not benefit from the intervention (see Table 1). These include: (1) psychological and sociodemographic variables; i.e. Type D personality, depression, anxiety, socio-economic status, age, gender, beliefs in medication, self-care behavior, and cognitive function; and (2) clinical variables; i.e., self-reported medication side effects; time since HF diagnosis; HF etiology; previous cardiac events (MI), previous cardiac procedures (PCI, CABG), previous cardiac devices (ICD, pacemaker), number of hospitalizations for HF; blood pressure; cholesterol; triglycerides; diabetes; atrial fibrillation; comorbidities; cardiac medication, other medication (including psychotropic medication); C-reactive protein; NT-pro-BNP; parameters measured in standard clinical practice (including liver function (ACAT, ALAT, Gamma GT), hemoglobin, hematocrit, leukocytes, and kidney function (urea and creatinine).

All endpoints will be assessed with standardized and validated measures shown to have good psychometric properties, usual care laboratory tests, physical examinations, and pharmacy refill records (Table 1).

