### Statistical analysis

This trial is designed to show whether the MASS device is effective in improving medication adherence in a chronic HF population compared to usual care only. Descriptive statistics (frequencies, means (±SD) will be calculated stratified by experimental group (intervention vs. usual care). T-tests for continuous variables and Chi-square tests for categorical variables will enable us to compare baseline values for both groups to formally test the successfulness of the randomization procedure. We will examine the effectiveness of the intervention by using the intention-to-treat principle, with the inclusion of all randomized participants in the statistical analyses regardless of whether they completed the intervention or the follow-up measurements. Missing data will be imputed using regression imputation techniques. The equality of subjective and objective adherence will be assessed by means of Intraclass correlation and Cohen's measure for agreement, the Kappa statistic, depending on the measure of adherence. Repeated measures analysis of covariance will be used to assess differences between the intervention and control group with respect to changes in adherence over the six-month intervention period, and to assess long-term effects (up to one year post-intervention) of the intervention on medication adherence, while taking potential confounders into account. To determine whether the time to hospitalization is longer for patients using the MASS device compared with patients in the control group, the log-rank test for comparison of Kaplan-Meier curves will be used. In addition, Cox proportional hazards regression modeling will be used to determine whether the usage of the MASS device predicts time to the first event (i.e. hospitalization due to HF or cardiac-related death). Multivariate regression analyses will be used to assess which psychological, clinical, demographic, and/or medication-related determinants predict adherence (with the percentage of adherence as dependent variable) in chronic HF patients and moderate the effects of the MASS device on patient adherence. The influence of potential effect modifiers will be examined by means of interaction terms.

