### Statistical power analysis

The most demanding analysis in this trial with regard to statistical power and sample size is the survival analysis in which adherence is a predictor of the number of HF-related hospitalizations. A power analysis in PASS for a Cox proportional hazard regression model [21] was performed, using information from the TweeSteden hospital and previous studies. Assuming an event rate of 29% (data 2008 and 2009, TweeSteden hospital), an estimated hazard ratio of between .70 and .80 [6], taking into account an SD of 1 for our main predictor adherence, and a correlation with covariating factors of on average .30, a two-sided type I error of .05, and a minimal power of 80% to detect a HR of .70, the sample size needed for this study to be sufficiently powered is 400. In an earlier study conducted at the same outpatient clinic and within the same patient population, a response rate of 78.3% was shown with a 19.9% attrition rate [22]. Thus, in order to achieve the calculated sample size of 400 patients, we intend to include 480 patients at baseline (1:1). Based on a more conservative response rate of 70%, 685 patients need to be approached. With 400 patients visiting the outpatient clinic each year (approximately 3-5 new patients/week) inclusion of such a number within two years is feasible. This sample size is also sufficient to test the other, less power demanding, research questions.

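### The arm comparison of time to hospitalization rests on an unstratified log-rank test and a Cox model with no baseline covariates fixed: valid, but it gives up power that T0 data already collected could supply

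*Protocol article*

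**What the plan says.** In the Statistical analysis section, the arms are compared on time to hospitalization as follows: "the log-rank test for comparison of Kaplan-Meier curves will be used". No strata are given. The next sentence adds that "Cox proportional hazards regression modeling will be used to determine whether the usage of the MASS device predicts time to the first event", the event being HF hospitalization or cardiac-related death. MASS use is the only predictor named, and the text calls the model neither adjusted nor unadjusted. Just before this, the repeated measures model for adherence is to be run "while taking potential confounders into account". The two survival sentences carry no such clause.

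The Study endpoints section lists, among the other secondary variables, "number of hospitalizations for HF; blood pressure; cholesterol; triglycerides; diabetes; atrial fibrillation; comorbidities" and "C-reactive protein; NT-pro-BNP; parameters measured in standard clinical practice", the last of these including creatinine. Three uses are given: checking the randomization, looking for moderators of adherence, and building risk profiles. The section on study procedures, randomization and follow-up places a blood draw, walk test, NYHA classification and echocardiography at T0 in both arms. It opens the allocation envelope only when the baseline assessments are complete.

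The Statistical power analysis section does assume covariates in a Cox model, with "a correlation with covariating factors of on average .30". The predictor in that model is adherence, not randomised arm: "taking into account an SD of 1 for our main predictor adherence".

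**The concern.** Number of hospitalizations is a main study parameter, and whether the device prevents hospitalization is one of the conclusions that the Discussion promises. In a hazard model, leaving out a variable that strongly predicts the event moves the treatment hazard ratio toward 1, even under perfect randomization, and lowers the power of the test. A log-rank test without strata has this property by construction.

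The variables that would recover the loss are measured before allocation, so adjusting for them is safe and needs no new data. If no set is fixed in advance, the Cox model also leaves open which of the many listed variables enter, and that choice could then be made with outcomes in view.

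**Working it through.** **Inputs from the article (Statistical power analysis).** Event rate 29%, with no time window given; hazard ratio .70 to .80 per SD of adherence; two-sided alpha .05; power 80% at .70; N = 400, with 480 to be enrolled; allocation 1:1.

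**Assumptions not in the article.** The .70 (or .80) is used as the arm effect, conditional on baseline risk. Baseline risk is one normal score whose log-hazard SD runs from 0.3 (weak) to 1.25 (strong). The C-index is about .63 at SD 0.5, .68 at 0.75, .72 at 1.0 and .76 at 1.25.

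**Step 1, the article's own figure.** For a continuous predictor, events D = (1.960 + 0.842)² / [SD² × (ln HR)² × (1 − R²)] and N = D / 0.29. With HR .70, (ln HR)² = 0.1272:
- R² = 0: D = 61.7, N = 213
- R² = .09 (r = .30): D = 67.8, N = 234
- R² = .30: D = 88.1, N = 304

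None of these gives 400. In any case the calculation concerns adherence and says nothing direct about the arm comparison.

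**Step 2, the arm comparison with nothing lost to omitted covariates.** Events at N = 400: 0.29 × 400 = 116. Power = Φ(√116 / 2 × |ln .70| − 1.960) = Φ(1.921 − 1.960) = 48%. For 80% power the Schoenfeld formula needs 4 × 7.849 / 0.1272 = 247 events, about 852 patients at 29%.

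**Step 3, the effect of adjustment.** Trials were simulated with exponential hazards, a common censoring time, 29% events overall and 4,000 runs per row. The arm-only Cox Wald test stands in for the log-rank test. N = 400, conditional HR .70:

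| Score SD | Arm only | Arm + score | Gain (points) | Arm-only HR |
|---|---|---|---|---|
| 0.3 | 45.1% | 46.0% | 0.9 | .705 |
| 0.5 | 45.3% | 47.8% | 2.5 | .708 |
| 0.75 | 42.4% | 48.8% | 6.4 | .720 |
| 1.0 | 35.6% | 47.3% | 11.7 | .741 |
| 1.25 | 31.4% | 48.2% | 16.9 | .757 |

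Monte Carlo error is about 1 point. As a cross-check, putting the diluted HR of .741 into the Step 2 formula gives Φ(1.614 − 1.960) = 36.5%, close to the simulated 35.6%.

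**Step 4, sensitivity.**
- Five estimated covariates in place of one known score, HR .70: gains of about 1 point (SD 0.3), 3 (0.5), 7 (0.75) and 13 to 15 (1.0 to 1.25).
- HR .80: about 2 to 7 points for moderate to strong scores, and about half a point at SD 0.3.
- N = 480, HR .70: gains of 1.5 to 17.7 points over SD 0.3 to 1.25, with adjusted power about 54% to 56%.
- 40% events, N = 400, HR .70: gains of 0.8 to 23.6 points over the same SDs.

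**The case against.** The strongest reply is that the article never calls the Cox model unadjusted. A Cox model with arm alone would largely repeat the log-rank test, and the sizing section shows that covariates in a Cox model were expected. A covariate list is normally left to the analysis plan, which is not shown. This stands in part. A reader might infer that the whole survival comparison ignores baseline risk; the text supports that only for the log-rank test. For the Cox model it supports no more than that no covariates are fixed. What remains is not mere missing detail, because the log-rank test is a stated choice and a more efficient one is available.

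A second reply is that the log-rank test is valid and the marginal hazard ratio is a legitimate target. That stands. A reader might take the shift toward 1 as bias; it is non-collapsibility, meaning that the marginal and conditional hazard ratios are different quantities. The point is about efficiency.

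A third reply is that the size depends on assumed prognostic strength. The eligibility criteria (stable HF, NYHA II-III, LVEF below 40%, no recent hospitalization) narrow the risk range and make the strong-score rows less secure. That also stands, and is why a range is given.

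**Conclusion.** The point holds as one of efficiency. The stated test of time to hospitalization discards prognostic information that the trial has in hand, and the accompanying Cox model fixes none of it.

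With the article's .70 taken as an arm effect, N = 400 and 29% events, the power at stake is about 1 point (weak score), 3 to 7 points (moderate) or 12 to 17 points (strong). At .80 it is about 2 to 7 points. No single figure within these ranges can be presented as a property of the plan, because the article gives no prognostic strength.

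A reader might also infer that adjustment would make this comparison adequately powered. It would not: adjusted power at .70 stays below 50% with 400 patients. Sizing on adherence instead of randomised arm is a separate and larger problem. The change is worth making because it is cheap, but the planned analysis is not invalid without it.

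**What to change.** Make the main arm comparison of time to first event a Cox model by intention to treat, with randomised arm plus a short set of T0 covariates. A reasonable set is log NT-proBNP, NYHA class, prior HF hospitalization (yes/no), LVEF and creatinine. Name the set before any outcome is seen. Keep the Kaplan-Meier curves and the unadjusted log-rank test as supporting analyses, and label the reported hazard ratio as conditional on the covariates.

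The cost is one or two sentences, with no new visits or measurements. Arm plus five covariates makes six parameters if NYHA II/III is one term, or about 19 events per parameter at 116 events (116 / 6). The downsides are small: the hazard ratio is conditional and needs that label, and a few missing baseline values need simple imputation, for which the plan already foresees regression methods.

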### Statistical power analysis

The most demanding analysis in this trial with regard to statistical power and sample size is the survival analysis in which adherence is a predictor of the number of HF-related hospitalizations. A power analysis in PASS for a Cox proportional hazard regression model [21] was performed, using information from the TweeSteden hospital and previous studies. Assuming an event rate of 29% (data 2008 and 2009, TweeSteden hospital), an estimated hazard ratio of between .70 and .80 [6], taking into account an SD of 1 for our main predictor adherence, and a correlation with covariating factors of on average .30, a two-sided type I error of .05, and a minimal power of 80% to detect a HR of .70, the sample size needed for this study to be sufficiently powered is 400. In an earlier study conducted at the same outpatient clinic and within the same patient population, a response rate of 78.3% was shown with a 19.9% attrition rate [22]. Thus, in order to achieve the calculated sample size of 400 patients, we intend to include 480 patients at baseline (1:1). Based on a more conservative response rate of 70%, 685 patients need to be approached. With 400 patients visiting the outpatient clinic each year (approximately 3-5 new patients/week) inclusion of such a number within two years is feasible. This sample size is also sufficient to test the other, less power demanding, research questions.

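### The sample size rests on adherence as a survival predictor, but the planned comparison of arms on hospitalization is more demanding at the same hazard ratio and falls short of 80% power at HR .70 to .80

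*Protocol article*

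**What the plan says.** The Statistical power analysis section of the Protocol article rests the sample size on one model: "The most demanding analysis in this trial with regard to statistical power and sample size is the survival analysis in which adherence is a predictor". The inputs are a 29% event rate from the hospital's own 2008 and 2009 data, "an estimated hazard ratio of between .70 and .80", "taking into account an SD of 1 for our main predictor adherence", "a correlation with covariating factors of on average .30", "a two-sided type I error of .05", and at least 80% power at HR .70. The result is 400 patients, raised to 480 at baseline for attrition. The section closes: "This sample size is also sufficient to test the other, less power demanding, research questions".

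The Statistical analysis section describes two survival analyses. One is a log-rank test of time to hospitalization, MASS against control. In the other, "Cox proportional hazards regression modeling will be used to determine whether the usage of the MASS device predicts time to the first event", where the event is HF hospitalization or cardiac-related death. Both compare the two randomised arms. No power is given for either. Hospitalizations are among the primary endpoints in the Abstract and the main parameters under Study endpoints.

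**The concern.** The information that a predictor carries in a Cox model is proportional to its variance. Adherence scaled to SD 1 has variance 1. A 1:1 arm indicator has variance 0.5 × 0.5 = 0.25. At equal HR the arm comparison therefore needs more events than the model used for sizing, which is the opposite of what the power section says about the ranking of its analyses.

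The Abstract says that the study will show whether telemonitoring is effective in preventing hospitalization. A reader told that the sample suffices for every other question would take a null arm result on hospitalization as evidence of no effect, when the trial may have had about an even chance, or less, of detecting a worthwhile one.

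**Working it through.** **Inputs** (Statistical power analysis section): event rate .29; HR .70 to .80; SD of adherence 1; correlation with covariates .30; two-sided alpha .05 (z = 1.96); power 80% (z = 0.8416); N = 400, or 480 at baseline; 1:1 allocation. The 18-month study period comes from the section on study procedures and follow-up.

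**1. The plan's own figure.** Events D = (1.96 + 0.8416)² / [SD² × (ln HR)² × (1 − R²)]. At HR .70, (ln HR)² = 0.1272 and the numerator is 7.849.

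- R² = 0: D = 61.7, N = 61.7/.29 = 213
- R² = .09 (.30 squared): D = 67.8, N = 234
- R² = .30 (.30 entered directly): D = 88.1, N = 304

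So 400 does not come out at exactly 80% power. With 400 patients (400 × .29 = 116 events) this model has 95.6% power (R² = .09) or 89.5% (R² = .30) at HR .70, which meets the stated minimum of 80%.

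**2. The arm comparison, events needed.** The same formula with variance 0.25 and no covariate term gives, at HR .70, D = 7.849/(0.25 × 0.1272) = 246.8, or about 247. N = 246.8/.29, about 851. Against the adherence model the ratio is 4 with R² = 0, 3.6 with R² = .09 and 2.8 with R² = .30.

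**3. The arm comparison, power available.** Power = Φ(√(D × 0.25) × |ln HR| − 1.96). The HRs are the adherence values carried over by assumption.

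| Patients | Events | HR .70 | HR .75 | HR .80 |
|---|---|---|---|---|
| 400 | 116 | 48% | 34% | 22% |
| 480 | 139 | 56% | 40% | 26% |

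Freedman's formula gives 47.6% where this one gives 48.4% (400 patients, HR .70).

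**4. Other readings of the 29%, at HR .70.** The plan states no time window for it.

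- Annual rate over 18 months (assumption): 1 − .71^1.5 = .402, so 161 or 193 events, and power is 62% (N = 400) or 70% (N = 480).
- Rate in the control arm only: the MASS arm would have 1 − .71^.70 = .213, a mean of .252, so 101 or 121 events, and power is 43% or 50%.

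**5. HR detectable with 80% power.** HR = exp(−2 × 2.8016/√D): .59 with 116 events and .62 with 139. With 161 or 193 events (annual reading) it is .64 or .67.

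**6. When the ranking would hold.** The arm test matches the sized-for model only if 0.5 × |ln HR(arm)| = |ln .70| × √(1 − R²). That means an arm HR of about .51 (R² = .09) or .55 (R² = .30).

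**7. A question for which the sufficiency claim can hold.** For adherence by arm as a simple comparison of two means, 200 per arm detects d = 2.8016 × √(2/200) = 0.28 with 80% power.

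**The case against.** The strongest reply is that the quoted HR belongs to adherence. The documents give none for MASS against usual care, so every power figure above for the arms borrows a value meant for something else. That stands, and the HR must be labelled an assumption. It does not rescue the claim. For the arm test to be no more demanding, the device would need an HR of about .51 to .55, and nothing in the article supports that. The Background cites telemonitoring reductions in readmissions and mortality of nearly one fifth. Read as an HR near .80 (an approximation), that gives 22% to 26% power.

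The event count is also uncertain. The 29% has no time window, and the Cox event adds cardiac death, which may raise the count by an amount that the documents do not give. The power is therefore a range, not a single figure.

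Four stronger readings are tempting and not supported:

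- *The trial cannot detect the effect that it quotes.* It can, for the predictor to which that effect belongs: 90% to 96% power at HR .70.
- *The adherence model does not belong to the trial.* The power section announces it, and it serves the primary objective on the effect of adherence on hospitalizations. Its absence from the Statistical analysis section is a detail that an article may leave to the full plan.
- *The figure of 400 is a miscalculation.* The 80% is stated as a minimum, and 400 exceeds it.
- *Power can be traced through the adherence gain from MASS.* The documents give no expected gain, so a figure built on one assumed shift, with all the effect passing through adherence, would have no basis.

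**Conclusion.** The point holds. The claim that the adherence model is the most demanding analysis is wrong at equal HR, and the general statement of sufficiency does not cover the randomised comparison on hospitalization, a primary endpoint.

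If the quoted HRs apply to the arms, power at the stated event rate is 48% to 56% at HR .70 and 22% to 26% at HR .80. Across all the readings of the 29% above, it is 43% to 70% at HR .70. The conclusion rests on proportional hazards, 1:1 allocation and an HR between arms no stronger than about .59 (about .67 on the most favourable reading of event rate and sample size). It does not show that any planned analysis is invalid, and it leaves open that the sample is adequate for adherence by arm.

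**What to change.** In the Statistical power analysis section:

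- Correct the statement about the most demanding analysis: it is the model used for sizing, and the arm comparison of time to hospitalization needs more events at the same HR.
- Limit the sufficiency statement to the questions for which it holds, such as adherence by arm.
- State the arm-comparison power as a range: 48% to 56% at HR .70, 34% to 40% at .75, 22% to 26% at .80, with a detectable HR of about .59 to .62. Label the HR an assumption. Give the time window of the 29%; if it is annual, give 62% to 70% at HR .70 and a detectable HR of about .64 to .67.

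In the Statistical analysis section, commit to reporting the arm HR with its 95% CI, so that a null result is read by the effects that it leaves open.

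The arithmetic does not require moving hospitalization to a secondary endpoint, or starting event follow-up at the end of the intervention, which would lose events. Those are separate trade-offs for the investigators. The cost is rewording and a less favourable power statement; no extra patients are needed.

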**Methods/Design:**

Consecutive patients with chronic, systolic HF presenting to the outpatient clinic of the TweeSteden Hospital, The Netherlands, will be approached for study participation and randomly assigned (1:1) following blocked randomization procedures to the intervention (n = 200) or usual care arm (n = 200). Patients in the intervention arm use the medication support device for six months in addition to usual care. Post-intervention, patients return to usual care only and all patients participate in four follow-up occasions over 12 months. Primary endpoints comprise objective and subjective medication adherence, healthcare consumption, number of hospitalizations, and cost-effectiveness. Secondary endpoints include disease severity, physical functioning, and QoL.

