### Study population and eligibility criteria

Consecutive patients with a diagnosis of chronic, systolic HF presenting to the HF outpatient clinic of the TweeSteden hospital Tilburg/Waalwijk, The Netherlands, will be approached for study participation and randomized to the intervention arm (n = 200) or usual care arm (n = 200) at inclusion. Eligible patients must (a) have a diagnosis of stable HF, (b) New York Heart Association (NYHA) functional class II-III, with a decreased pump function (left ventricular ejection fraction (LVEF) < 40%), (c) titrated to the most optimal doses of ACE-inhibitor or angiotensin receptor blocker (ARB), and beta-blocker, (d) receiving stable doses of at least three HF medications for one month with no plans to add or adjust HF medications or titrate further in the immediate future, and (e) providing written informed consent.

Exclusion criteria are: (a) age < 50 years, (b) diastolic HF (intact pump function), (c) either myocardial infarction, or invasive treatment (percutaneous coronary intervention (PCI) or coronary artery bypass grafting (CABG)), or hospitalization within one month prior to inclusion, (d) participation in another clinical trial, (e) life-threatening co-morbid conditions (e.g., cancer), (f) diminished mental capacities (suspected serious cognitive decline will be confirmed by a Mini Mental State Examination (MMSE score ≤24 [19])), (g) a history of psychiatric disorders apart from affective disorders (depression and anxiety disorders), (h) significant sight and/or hearing impairment, and (i) insufficient knowledge of the Dutch language.

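### The protocol gives two randomized totals, 400 and 480, and 480 leaves about 384 patients, not 400, after the cited 19.9% attrition

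*Protocol article*

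**What the plan says.** The size of the trial is given in three places in the protocol article.

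- Abstract, Methods/Design: patients are "randomly assigned (1:1) following blocked randomization procedures to the intervention (n = 200) or usual care arm (n = 200"), a total of 400.
- Study population and eligibility criteria: patients are "randomized to the intervention arm (n = 200) or usual care arm (n = 200) at inclusion", again 400.
- Statistical power analysis: "the sample size needed for this study to be sufficiently powered is 400". An earlier study at the same clinic is then cited, in which "a response rate of 78.3% was shown with a 19.9% attrition rate". The section concludes: "Thus, in order to achieve the calculated sample size of 400 patients, we intend to include 480 patients at baseline (1:1"). It continues: "Based on a more conservative response rate of 70%, 685 patients need to be approached".

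The Statistical analysis section plans an intention-to-treat analysis of all randomized patients, completers or not, with imputation of missing data. Table 1 takes rehospitalisations and time to first HF-related hospitalization from medical records at every time point.

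**The concern.** There are two separate problems.

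First, 400 and 480 are both stated as the number entering the trial with 1:1 allocation. The randomized total tells the team when recruitment is complete, and readers will later compare it with the size achieved. A gap of 80 patients leaves both uncertain.

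Second, the step from 400 to 480 is presented as the allowance for attrition, but it does not give the result claimed for it. A reader who takes the paragraph at its word would expect 400 patients at the end of follow-up. On the cited attrition, neither total gives that.

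**Working it through.** **Inputs, all from the Statistical power analysis section unless noted**

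- Required number: 400.
- Attrition: 19.9%, so the retained fraction is 1 − 0.199 = 0.801.
- Planned at baseline: 480, 1:1.
- Conservative response rate: 70%; number to approach: 685.
- Cox inputs: event rate 29%, SD of adherence 1, average correlation with covariates 0.30, two-sided alpha 0.05, hazard ratio 0.70, minimum power 80%.
- Randomized total in the abstract and the eligibility section: 200 + 200 = 400.

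**Reproducing the plan's own figures**

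- 400 × 1.199 = 479.6, which rounds up to 480; 400 × 1.2 = 480 exactly. The stated 480 is therefore consistent with adding the attrition percentage to the target. The article shows no formula, so this mechanism is an inference.
- 480/0.70 = 685.7, which matches the 685 to approach. Starting from 400 would give 400/0.70 = 571.4, which does not. The recruitment plan in this section is therefore built on 480.

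**Does 480 leave 400?**

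- Remaining = N × (1 − attrition). 480 × 0.801 = 384.5, so about 384, some 16 short of 400 (about 4%).
- 480 leaves 400 only if attrition is no more than 1 − 400/480 = 16.7%, below the cited 19.9%.
- Needed at baseline = target/(1 − attrition). 400/0.801 = 499.4, so 500 (250 per arm).
- If 400 are randomized, as the other two sections say: 400 × 0.801 = 320.4, so about 320, some 80 short (20%).

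**What this means for the stated power**

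For a Cox model with a continuous predictor, power = Φ(√[N × 0.29 × (1 − R²)] × SD × |ln HR| − 1.96), with SD = 1 and |ln 0.70| = 0.357. The correlation of 0.30 can be read as R² = 0.30² = 0.09, or as R² = 0.30 directly. Both are shown.

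| Patients | R² = 0.09 | R² = 0.30 |
|---|---|---|
| 320 | 91% | 82% |
| 384 | 95% | 88% |
| 400 | 96% | 90% |

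As an example, for N = 320 and R² = 0.30: 320 × 0.29 × 0.70 = 64.96; √64.96 = 8.06; 8.06 × 0.357 = 2.87; 2.87 − 1.96 = 0.91; Φ(0.91) = 0.82.

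Every entry is above 80%. These figures apply only to the analysis that the protocol sized, in which adherence is a continuous predictor of hospitalization.

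**The case against.** **The 200 per arm might be the number left after attrition.** This would reconcile the totals, but the eligibility section ties 200 per arm to randomization at inclusion, and the power section attaches the 1:1 ratio to the 480. Under Study procedures, the allocation envelopes are opened at the baseline visit once the assessments are done, so patients included at baseline and patients randomized are in practice the same group. The reading does not hold.

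**The intended total can be identified.** This is largely right. Only 480 is described as the intended baseline number, the 685 is derived from it, and nothing in the article instructs recruitment to stop at 400. The likeliest explanation is that the abstract and the eligibility section carry the uninflated figure. The inconsistency remains, but it is easily resolved.

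**Patients who drop out are not lost to the analysis.** This also stands. All randomized patients are to be analysed, a patient who leaves contributes censored time to the Cox model, and hospitalizations are taken from medical records, so a missed visit need not lose the event. For the analysis that drives the sample size, 384 and 320 are therefore pessimistic counts. Still, the protocol itself chose to inflate for attrition, and that step should give the number it claims.

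**A reader might infer that the trial is underpowered.** The documents do not support that. The promise is at least 80% power at a hazard ratio of 0.70, and on the protocol's own inputs this is met even with 320 patients. The protocol also mentions hazard ratios up to 0.80, where power is lower (44–54% at 320, 50–61% at 384, 52–63% at 400), but it does not promise 80% there, and 400 patients would not provide it either.

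**Conclusion.** Both parts hold. The protocol states two randomized totals that differ by 80 patients. The larger one falls about 16 short of the 400 that it is said to achieve: 480 leaves about 384, and 500 would be needed. With 400 randomized, about 320 would complete.

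The conflict between 400 and 480 is the weightier part; the inflation error alone is small. Neither is a shown loss of the stated power. Severity is moderate: a figure that the trial relies on is wrong as written, but the correction is simple and the conclusion about power at a hazard ratio of 0.70 survives it.

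The completer counts assume that the 19.9% from the earlier study applies over the follow-up of this trial, as the protocol itself assumes. The power figures assume that the 29% event rate applies to the number of patients used, and that R² is either 0.09 or 0.30.

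**What to change.** State one randomized total in the abstract, in Study population and eligibility criteria, and in Statistical power analysis.

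- **Cheapest version:** keep 480. Change 200 per arm to 240 per arm in the abstract and the eligibility section. In the power section, say that about 384 are expected to complete follow-up after 19.9% attrition, and restate the power for that number. The 685 to approach can stay. The cost is a text correction in three places and an expected number of completers that falls from 400 to 384.
- **If 400 must remain after attrition:** randomize 500 (250 per arm) and approach 500/0.70 = 714.3, so 715. That is 20 more patients randomized and 30 more approached, and the statement that recruitment is feasible within two years would need to be checked against those numbers.

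In either version, show the attrition formula so that the total can be checked.
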